### 378 9.3 Risk/Benefit Analysis

379  
380 Patients may benefit from participation in this study. Results will be  
381 provided to the treating physician, and may lead to a change in treatment  
382 of prostate cancer. Although such a change would be expected to benefit  
383 patients, it is also possible that a change in treatment will lead to side  
384 effects.

## 385 386 10.0 ETHICS

387  
388 10.1 The study will be submitted for initial and ongoing annual REB review.  
389 Study related procedures will not commence prior to receipt of REB approval.

390  
391 10.2 Any amendment to the study will be submitted for review by the REB  
392 before any changes are implemented unless required to eliminate immediate  
393 hazard to the study participants.

394  
395 10.3 Data derived from this study may be reported in scientific publications.  
396 Patients will not be indicated by name.

397  
398 10.4 Sample size determination

399 This study will employ a cmRCT design to determine the potential benefit of  
400 PSMA-PET guided radiotherapy in patient with high-risk of micro/oligo

metastatic disease. Patients will be randomly selected (1:1) for this intervention from the PERA study if they provide consent and meet eligibility criteria. The study will be designed with an  $\alpha=0.1$  and 80% power (as recommended for phase II randomized trials) for the primary outcomes. Patients will be stratified according to institution and category at time of enrollment (oligometastatic - estimated 15% of cohort) vs. high-risk localized – estimated 35% of cohort, vs. recurrent post RT – estimated 5% of cohort vs. recurrent post RP – estimated 45% of cohort).

Literature suggests that PSMA PET/CT can increase the diagnostic yield (sensitivity) for bone metastases by 10-15% compared with standard staging (approximately 85% to 99%), and for lymph node metastases by 50% (25% to 75%), resulting in over 60% of patient with high-risk of metastases demonstrating new identifiable lesions on PSMA PET. Adjusting for the proportion surviving free of failure at 5 years within the strata (0.05, 0.6, 0.3, and 0.4, respectively), a total of 130 patients receiving a PSMA -PET/CT evaluation (and 130 control) will be required to demonstrate benefit over standard care ( $\alpha=0.1$ ,  $\beta=0.8$ , one-tailed, HR 1.4).

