[18F]DCFPyL is a promising high-sensitivity second generation PSMA-targeted urea-based PET probe. Studies employing second-generation PSMA PET/CT imaging in men with biochemical progression after definitive therapy suggest detection of metastases in over 60% of men imaged.[3] In fact, PSMA-based PET has so far proven to have higher sensitivity than any other modality for localization of the site of recurrence. Applications that show promise and require further investigation include the characterization and risk stratification of primary PCa, complete staging of metastatic PCa to allow for PSMA-targeted radiotherapy and improved identification of patients with oligometastatic disease. One of the main advantage of this new PET tracer is that it is labeled with Fluor-18 instead of Gallium-68, which is the most commonly used ligand

in other PSMA targeted probes. The radionuclide F-18 has several physical advantages compared to Ga-68, including lower energy and shorter positron range providing higher image resolution, longer half-life (110min vs. 68min) enabling multiple scans from a single formulation, and shipment to other sites without radiochemistry/cyclotron capability.

Here we hypothesize that definitive RT informed by PSMA-PET findings will lead to improved cancer control outcomes compared with RT guided by conventional staging only. We will utilize a cmRCT design, where eligible patients will be randomly selected for PSMA-PET/CT imaging prior to RT and approached for this investigational study. This study will therefore be conducted in companion to PERA (Partnership initiative for the Evaluation of technological innovation in Radiotherapy, CHUM CER 17.032).

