## **3.0 Eligibility Assessments**

### **3.1 Inclusion criteria**

- 3.1.1 Enrolled in PERa registry (CHUM CER 17.032), consented to contact for investigational trials, consented to serve as control, and randomly selected to be offered the experimental intervention.

- 3.1.2 Histological diagnosis of prostate cancer planned for definitive-intent radiotherapy.
- 3.1.3 ECOG 0-1
- 3.1.4 Charlson Cormobidity Index  $\leq 4$
- 3.1.5 High-risk of distant metastases as defined by any of:
- 3.1.5.1 Oligometastases ( $\leq 5$ ) (regional or distant) identified on conventional staging, with  $\leq 3$  metastasis in any non-bone organ. For a spine metastasis, direct involvement of adjacent spinal segments would still be considered as “one” tumour. For nodal metastases, more than one involved lymph node in the same ipsilateral nodal region/chain would still count as “one” tumour. Defined nodal regions for this protocol include inguinal, external iliac, internal iliac, common iliac, retroperitoneal, hilar/mediastinal, anterior cervical, posterior cervical, and axillary. Metastases in all other organs that are within 1cm of each other will be considered as “one” tumour.
  - 3.1.5.2 Subjects with newly diagnosed high-risk (NCCN) localized prostate cancer and CAPRA score 6-10.
  - 3.1.5.3 Subjects with a prior history of treated prostate cancer
    - Post-radical prostatectomy and biochemical failure ( $> 0.1\text{ng/ml}$ )
    - Post-curative radiotherapy and biochemical failure (Phoenix-RT)

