## 4.0 Enrollment procedures

- 4.1 Confirmation of patient`s eligibility
- 4.2 Enrollment will occur after consent is completed.
- 4.3 Study Registration
- 4.3.1 Registration will occur only after pre-treatment evaluations and informed consent are completed.

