## 6.0 Study Implementation

### 6.1 Study Design

6.1.1 Nested within the Partnership Initiative for the Evaluation of Technological Innovation in Radiotherapy (PERA - NCT03378856) prospective cohort, we will perform a Randomized Controlled Trial (RCT) comparing PSMA-guided radiotherapy (PSMAgRT) to controls.

When entering the PERA cohort, consent is asked for the use of data and for being approached for future research. Random selection of eligible patients to this trial were offered PSMAgRT. Outcomes will be compared with eligible patients randomized to a control arm and receiving usual care.

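### The experimental arm is counted by PET receipt after a consent step that controls do not face, so the protocol supports two different primary comparisons and its sample size makes no allowance for refusal

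*Protocol*

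**What the plan says.** **Order of events.** The Introduction states that "eligible patients will be randomly selected for PSMA-PET/CT imaging prior to RT and approached for this investigational study", so selection comes before the approach. Section 4.2 adds: "Enrollment will occur after consent is completed". Section 4.3.1 places registration after both the pre-treatment evaluations and informed consent.

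**Entry criterion.** Section 3.1.1 requires registry enrolment, consent to contact and consent to serve as a control. It also requires that the patient was "randomly selected to be offered the experimental intervention".

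**Target.** The synopsis gives 130 experimental subjects. Section 10.4 says what is counted: "a total of 130 patients receiving a PSMA -PET/CT evaluation (and 130 control) will be required". Selection is 1:1, with alpha 0.1 and 80% power, "one-tailed, HR 1.4". No number to be offered the PET, no refusal rate and no rule for decliners is given.

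**Comparison.** Section 6.1.1 describes the experimental group as patients who were offered PSMA-guided radiotherapy, and continues: "Outcomes will be compared with eligible patients randomized to a control arm and receiving usual care". Section 10.5 uses randomised patients as the denominator for the interim analysis of the primary endpoint.

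**The concern.** In a cohort design that selects first and seeks consent second, only the selected patients get the chance to refuse. If the experimental arm consists of those who accepted and were scanned, it has been filtered. The controls have not, because the patients among them who would have refused are never asked and stay in. Those who accept may differ from those who decline in fitness, urgency of treatment or adherence, all of which can bear on failure-free survival.

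Two things are at stake. The first is whether the primary comparison keeps the protection of randomisation. That depends on whether the count in 10.4 or the wording of 6.1.1 and 10.5 defines the arms. The second is power: if all selected patients are analysed as allocated, decliners dilute the effect, and 10.4 leaves no room for that.

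The wording of 3.1.1 adds to the ambiguity. Being selected for the offer is listed as a condition of eligibility, so read literally no control is eligible, although 6.1.1 describes the controls as eligible patients.

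**Working it through.** **1. Reproducing the stated size**

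Inputs from 10.4:
- Stratum shares 0.15, 0.35, 0.05 and 0.45, with 5-year failure-free proportions 0.05, 0.6, 0.3 and 0.4.
- One-sided alpha 0.10, power 80%, HR 1.4 (control relative to PSMA).

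Inputs from elsewhere: 3-year enrolment (synopsis) and 5 years of follow-up (synopsis and withdrawal criteria).

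Weighted control proportion at 5 years: 0.15×0.05 + 0.35×0.6 + 0.05×0.3 + 0.45×0.4 = 0.4125.

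Events (Schoenfeld): D = 4(z₀.₉₀ + z₀.₈₀)² / (ln 1.4)² = 4(1.2816 + 0.8416)² / 0.3365² = 159.3, rounded up to 160.

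Event probabilities assume exponential failure within each stratum.

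| Follow-up | Control | PSMA | Mean | N = 160/mean | Power at 260 |
|---|---|---|---|---|---|
| Uniform 3-year accrual, 5 years after last entry | 0.667 | 0.562 | 0.614 | 261 | 80.1% |
| Exactly 5 years per patient | 0.588 | 0.484 | 0.536 | 299 | 75.9% |

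The first row matches the stated 260. Both rows give every experimental patient the full HR of 1.4, which means zero refusal.

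**2. Offers needed for 130 recipients**

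The documents give no refusal rate r, so 10% and 20% are assumed. Offers = 130/(1 − r): 130/0.9 = 144.4, so 145; 130/0.8 = 162.5, so 163. Under 1:1 selection, the matching control group would be 145 or 163, not 130. The pairing of 130 recipients with 130 controls fits 1:1 selection only if nobody declines or if decliners are replaced.

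**3. Power when all selected patients are analysed as allocated, 130 randomised per arm**

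Assume that decliners have the control hazard. Then approximately:
- log HR = (1 − r) × ln 1.4
- experimental event probability = (1 − r)p_PSMA + r·p_control
- power = Φ(√D/2 × log HR − 1.2816), where D is the expected number of events

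| Follow-up | r | HR | D | Power | Total N for 80% |
|---|---|---|---|---|---|
| 3 + 5 years | 0 | 1.400 | 159.7 | 80% | 261 |
| 3 + 5 years | 10% | 1.354 | 161.0 | 74% | 319 |
| 3 + 5 years | 20% | 1.309 | 162.4 | 67% | 399 |
| Exactly 5 years | 0 | 1.400 | 139.3 | 76% | 299 |
| Exactly 5 years | 10% | 1.354 | 140.7 | 70% | 365 |
| Exactly 5 years | 20% | 1.309 | 142.0 | 63% | 456 |

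Example (3 + 5 years, r = 10%): √161.0/2 × 0.3028 − 1.2816 = 0.640, and Φ(0.640) = 0.739.

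The drop from 80% to 76% between the two zero-refusal rows comes from follow-up, not from refusal. The loss due to refusal is read within each follow-up pattern.

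**4. Error rate if decliners were omitted from the experimental arm only**

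This is conditional: the protocol does not state such an omission. It was simulated with no true effect, 130 per arm, exponential failure, 5 years of follow-up and a one-sided 10% test. Refusal rates and decliner hazards are assumed.
- 10% refusal, decliner hazard 1.5 times that of acceptors: error about 15%.
- 20% refusal, 1.5 times: about 20–23%, depending on simulation details.
- 20% refusal, 2 times: about 31–35%.
- 20% refusal, 0.67 times: about 4–5%, with the bias now against PSMA.

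The direction reverses within a plausible range, so the sign of any bias cannot be predicted.

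**The case against.** A reader might infer that refusers leave one arm only and that randomisation is therefore broken. The document does not support that.
- No section drops decliners from the failure-free survival comparison. The sentence in 10.4 is a sample-size count, not an analysis rule.
- Section 6.1.1 speaks of those offered, and 10.5 of those randomised. Both fit an analysis as allocated.
- Cohort consent covers use of data, so decliners remain analysable.
- The condition in 10.4 that patients provide consent may mean registry consent, and eligibility can be read as settled before selection.
- An analysis population is commonly defined in a SAP, and none is shown here.
- Section 3.1.1 can be read as governing entry to the offered intervention only.

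All of this stands against the stronger reading, and it makes the error rates in step 4 illustrative only. It does not remove the narrower point. The accrual target, the entry criterion and the refusal assumption are stated in this protocol, and a SAP would not change them. If recruitment stops at 130 scanned and 130 controls, an as-allocated analysis is no longer 130 against 130 unless nobody declines.

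It could also be said that HR 1.4 was meant as the effect of the offer, with refusal already included. In that case 130 randomised per arm would need no dilution. Section 10.4 does not say so: it argues from what the PET detects and ties the 130 to patients receiving it.

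**Conclusion.** The point holds in limited form. The protocol counts one arm by PET receipt after selection and the other by randomisation, while its design and interim sections imply all selected patients. It therefore supports two different primary comparisons. Comparing recipients with all controls is open to selection bias of unknown size and direction unless nobody declines. It is not established that the trial will be analysed that way.

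On power, the stated 80% rests on zero refusal. At an assumed 10% or 20% refusal, 130 randomised per arm gives about 74% or 67% with 3-year accrual plus 5 years after last entry. With exactly 5 years per patient it gives about 70% or 63%, against 76% without refusal. These figures assume that HR 1.4 applies to recipients, that decliners have the control hazard, and that failure is exponential within strata.

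**What to change.** 1. In 10.4 and the synopsis, state the target as patients randomised per arm (130 to the offer, 130 to control) and restate power at the expected uptake, with that uptake given as an explicit assumption.
2. In 6.1.1, state that the primary failure-free survival comparison includes all eligible patients randomly selected, in their allocated arm, whether or not they accept the PET.
3. Apply the same eligibility criteria to both arms before selection, and move the clause on selection for the offer out of 3.1.1 into the description of allocation.

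Reporting uptake would help readers interpret the result. A complier-average analysis is optional.

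The cost is mainly wording, since decliners are in the cohort with consent to use of their data. The downside is that the stated power becomes somewhat less favourable. Holding 80% would take about 319 or 399 patients in total at 10% or 20% refusal under the accrual pattern that reproduces 260.

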## 10.5 Interim analysis

2.2.6 An interim analysis will be conducted upon the completion of accrual to assess the rate of new lesion detection and its impact on prostate cancer management.

2.2.7 An interim analysis for the primary endpoint will be conducted when 25% of randomized patients have experienced a failure event within a stratified cohort. The purpose of this analysis is to guide the design of a subsequent phase III trial, including which strata should be included in a next phase clinical trial. The efficacy criterion for the interim analysis will be a two-sided p-value threshold of 0.05 for each individual strata.

## 11.0 DATA HANDLING AND RECORD KEEPING

Data will be recorded and stored using the following sources:

11.1 Medical records (OASIS, MOSAIC): clinical data

11.2 PACS: imaging data

All records and documents pertaining to the study will be retained by the study trial site for at least 25 years from the completion of the study, and will be available for inspection by Health Canada, institutional representatives (REB, Quality Assurance) and other regulatory bodies.

Coded imaging data may also be shared with industry or academic collaborators outside the institution. The details of this data exchange will be described in separate Data Transfer Agreements (DTAs) between institution and these parties.

Data will not be shared with any external collaborator except the appropriate agreements are in place. Hard copy study files will be kept secured. All computerized files will be password protected and no laptop will be used. Coded research data will be stored on research servers.

Diffusion - aggregate disclosure to study participants and presentation of results at conferences and scientific publications. Participants will not be identifiable in any knowledge transfer.

## Appendix 1: Guide – Definitive Radiotherapy to Oligometastatic Prostate Cancer

The following doses are meant as a guide. For SABR, it is strongly recommended that patients be referred to a center of expertise for treatment.

### Recommended Dose/Fractionation of Definitive RT

- Prostate: EQD2 ( $\alpha/\beta=3$ )=72Gy or more
- Involved lymph nodes: 35-50 Gy in 5 fractions, or a simultaneous integrated boost to pelvic RT (EQD2=66-70Gy,  $\alpha/\beta=3$ )
- Bone metastases: 30-40 Gy/5 fractions, or a simultaneous integrated boost to pelvic RT (EQD2=66-70Gy,  $\alpha/\beta=3$ )
- Lung Metastases (peripheral) : 48-60 Gy / 4 fractions OR 54-60 Gy / 3 fractions
- Lung Metastases (central): 50Gy/5 fractions or 60Gy/8 fractions
- Liver Metastases: 30-60 Gy in 3-5 fractions
- Adrenal/spleen metastases: 35-50Gy in 5 fractions
- Soft tissue metastases not otherwise classifiable: 35-50 Gy in 5 fractions.
